#### Primary outcome

2.12.1

The main primary outcome is the NT-proBNP responder rate at week 12, defined as a decrease in NT-proBNP exceeding 30% from baseline. Collect fasting plasma from subjects and measure NT-proBNP levels following the reference kit protocol. The six-minute walk test assessed exercise tolerance by having patients walk as far as possible on a flat corridor within 6 min. Distances were categorized as: <150 m: Severe heart failure; 150–450 m: Moderate heart failure; >450 m: Mild heart failure.

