#### Safety assessment

2.12.3

This trial will assess safety by monitoring adverse events (AEs), serious adverse events (SAEs), and discontinuation or treatment modifications due to AEs. Safety assessments at weeks 0, 4 and 12 will include vital signs, blood/urine/stool routine testing, 12-lead ECG, liver function, renal function, coagulation testing, and electrolytes including serum potassium and sodium; echocardiography and chest radiography are performed at weeks 0 and 12. All AEs will be graded from I (mild) to V (fatal), assessed for relationship to study treatment using the prespecified five-category causality scale, and followed until resolution, return to baseline or stabilization. SAEs will be reported to the monitor, coordinating center and manufacturer within 24 h. Independent monitors and auditors will oversee protocol adherence, source-data verification and safety reporting; this oversight is used instead of a separate data safety monitoring committee.

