### Data analysis and statistical methods

2.15

SPSS 24.0 software will be used to perform statistical analysis on the collected data. All statistical tests will be two-tailed, with a *P*-value ≤ 0.05 indicating statistical significance for the tested difference. Descriptive analysis: Categorical indicators will describe the number and percentage of cases in each category. Quantitative indicators will be described using mean, standard deviation, maximum value, minimum value, median, lower quartile (Q1), and upper quartile (Q3). Comparisons between two groups of general characteristics will be analyzed using appropriate methods based on the type of indicator. For quantitative data, between-group comparisons will employ paired t-tests or Wilcoxon signed-rank tests. For categorical data, chi-square tests or exact probability methods will be used. For ordinal data, Wilcoxon signed-rank tests or the Mann–Whitney U (MWU) test will be applied. Age, atrial fibrillation status and estimated glomerular filtration rate will be recorded at baseline and examined in covariate-adjusted and sensitivity analyses because these factors can materially alter NT-proBNP concentrations. Time to first event will be displayed with Kaplan–Meier curves, compared by the log-rank test, and modeled using Cox regression to estimate hazard ratios (HRs) with 95% confidence intervals. Event counts and recurrent rehospitalizations will be summarized descriptively by group.

The Full Analysis Set (FAS) followed the intention-to-treat principle, including all randomized subjects who received at least one dose of the study drug, with exclusions limited to major protocol violations, no study drug exposure, or complete lack of post-randomization data. The per-protocol set (participants with ≥80% adherence, primary endpoint data and no major protocol violation) will support sensitivity analyses, and the safety set will include all randomized participants who received at least one dose and had a safety assessment. For missing co-primary endpoint data, the prespecified conservative worst-case approach will be used in the primary FAS analysis. Missing data amount, reasons and patterns will be reported by group. Multiple imputation under a missing-at-random assumption will be used as a sensitivity analysis, with additional best/worst-case analyses to evaluate departures from that assumption.

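### The full analysis set is labelled intention-to-treat but drops major protocol violators and patients with no post-randomization data, so the primary comparison is not fully protected by randomization

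*Protocol article*

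**What the plan says.** All the relevant definitions stand in Section 2.15 of the protocol article.

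- **Principle and entry:** "The Full Analysis Set (FAS) followed the intention-to-treat principle, including all randomized subjects who received at least one dose of the study drug".
- **Exclusions, in the same sentence:** "with exclusions limited to major protocol violations, no study drug exposure, or complete lack of post-randomization data".
- **Per-protocol set:** "participants with ≥80% adherence, primary endpoint data and no major protocol violation". It supports sensitivity analyses.
- **Missing outcomes in the primary analysis:** "For missing co-primary endpoint data, the prespecified conservative worst-case approach will be used in the primary FAS analysis".
- **Missing-data sensitivity analyses:** "Multiple imputation under a missing-at-random assumption will be used as a sensitivity analysis, with additional best/worst-case analyses". The text does not say that these go beyond the FAS.
- **Safety set:** "the safety set will include all randomized participants who received at least one dose and had a safety assessment".

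The outcome concerned is set in Section 2.12.1: "The main primary outcome is the NT-proBNP responder rate at week 12". Section 2.12.3 schedules an earlier visit after randomization: "Safety assessments at weeks 0, 4 and 12 will include vital signs".

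**The concern.** Intention-to-treat keeps randomized patients in the comparison whatever happens to them afterwards. The FAS sentence states that principle and then departs from it in two ways beyond the familiar one-dose condition.

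The more serious departure is the violator exclusion. As written it takes in any major violation, including one that arises during treatment. Such a violation can depend on how the patient fares on QSG or placebo, so removing violators can make the groups unlike each other. The per-protocol set removes the same patients. Comparing the two analyses therefore says nothing about the effect of leaving violators out; only adherence and availability of the endpoint separate the sets.

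The second departure is the removal of patients with no data at all after randomization. They are the clearest case for a conservative missing-outcome rule, yet they are gone before the rule is applied.

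At stake is the validity of the primary responder comparison: its estimate and its type I error.

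**Working it through.** **1. The plan's own figure.** Section 2.3 gives 53% against 33%, α = 0.05, β = 0.2 and 15% dropout; Section 2.15 makes tests two-tailed. With unpooled variance:

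n = (1.960 + 0.842)² × (0.53 × 0.47 + 0.33 × 0.67) / 0.20² = 92.3, so 93 per arm.

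93 / 0.85 = 109.4, so 110. The stated 110 per group is reproduced and the sample size is not in dispute.

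**2. Who is kept and who is removed under Section 2.15.**

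| Randomized, dosed patient | In FAS? | Reached by worst-case rule? | In per-protocol set? |
|---|---|---|---|
| Week-12 value, no major violation | Yes | Not needed | Yes, if adherence is at least 80% |
| Some post-randomization data, no week-12 value | Yes | Yes | No |
| No post-randomization data | No | No | No |
| Major violator, even with a week-12 value | No | No | No |

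The last two rows contradict the stated principle.

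**3. Illustration of bias when there is no treatment effect.** Assumptions: true response 33% in both arms (the plan's placebo rate), 110 per arm, every excluded patient a non-responder. With excluded shares d₁ (QSG) and d₀ (placebo):

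- apparent rates pᵢ = 0.33 / (1 − dᵢ), on nᵢ = 110 × (1 − dᵢ) patients;
- spurious difference Δ = p₁ − p₀;
- pooled-variance z-test at 1.96, with chance of rejection Φ((Δ − 1.96·SE₀)/SE₁) + Φ((−Δ − 1.96·SE₀)/SE₁), where SE₀ uses the pooled rate and SE₁ the separate rates.

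For 10% against 5%: p₁ = 0.33/0.90 = 36.7% on 99 patients, p₀ = 0.33/0.95 = 34.7% on 104.5, Δ = 1.9 points. SE₀ and SE₁ are both 0.0672. The chance of rejection is 0.0472 in favour of QSG plus 0.0123 in favour of placebo, about 0.060.

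| Excluded, QSG / placebo | Apparent rates | Spurious difference | Two-sided error |
|---|---|---|---|
| 5% / 5% | 34.7% / 34.7% | 0 | 5.0% |
| 10% / 5% | 36.7% / 34.7% | +1.9 points | 6.0% |
| 10% / 0% | 36.7% / 33.0% | +3.7 points | 8.6% |
| 15% / 5% | 38.8% / 34.7% | +4.1 points | 9.2% |

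**4. What keeping the patients would cost.** Assumptions: the planned rates of 53% and 33%, a share d per arm without a week-12 value, and worst case read as non-response in both arms. Keeping everyone gives rates 0.53(1 − d) and 0.33(1 − d) on 110 per arm. Removing them leaves 53% and 33% on 110(1 − d).

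| d per arm | Rates, all kept | Power, all kept | Power, removed |
|---|---|---|---|
| 5% | 50.4% / 31.4% | 82.2% | 83.7% |
| 10% | 47.7% / 29.7% | 78.7% | 81.6% |
| 15% | 45.1% / 28.1% | 74.8% | 79.4% |

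At 15%, 80% power with everyone kept needs about 125 per arm. Only patients with no post-randomization data would change status because of a missing value, since ordinary dropouts already stay in the FAS. The relevant d is their share alone. Violators with a week-12 value would enter with that value.

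**The case against.** Much can be said for the plan, and several stronger readings fail.

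A reader might infer that the worst-case rule is disabled. It is only narrowed. The exclusion requires that nothing was recorded after randomization, and the article leaves many chances for a record: the week-4 visit (Section 2.12.3), contacts and hospital-record review at weeks 26 and 52 (2.12.4), and a final assessment and follow-up of withdrawn patients (2.7). A patient who stops for an adverse event must have that entered in the case report form, which is itself post-randomization data. Such a patient is not lost under the no-data criterion. Few patients should be.

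A reader might also infer that a dosed patient who dies early vanishes from the safety set. Section 2.12.3 counts adverse and serious adverse events as part of the safety assessment, with a grade for fatal events and reporting within 24 hours. A reported death is safety information, so only unclear wording remains.

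The 15% dropout in Section 2.3 might be taken as the expected exclusion rate. It is not: a dropout with any later data stays in the FAS.

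The definition of a major violation may stand in the full protocol or analysis plan, and its absence from a condensed article is no fault. It might cover only eligibility errors found after randomization. But the sentence that is published sets no such limit and declares the set intention-to-treat.

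It is also true that a per-protocol set normally lies within the FAS, that adherence and endpoint data still distinguish the two here, and that removing patients without data is a common, openly stated modified intention-to-treat choice. Double-blinding (2.9) makes unequal exclusion less likely. Missing data will be reported by group, with multiple imputation and best/worst-case analyses. These points reduce the concern about the no-data exclusion. They do not justify an unrestricted violator exclusion.

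**Conclusion.** The point holds and should be fixed. The FAS rule contradicts its own stated principle, chiefly through the violator exclusion and less so through the no-data exclusion. Following it could bias the primary comparison.

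The size is unknown. The illustrative two-sided errors, from 6.0% to 9.2% against a nominal 5%, need exclusion to differ between arms and take every excluded patient as a non-responder, which is an upper case. With equal exclusion under the same assumptions there is no bias. The article neither gives exclusion rates nor shows that any imbalance is expected, so these figures show what the rule permits and are not a forecast.

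**What to change.** In Section 2.15:

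1. Delete major protocol violations and absence of post-randomization data from the FAS exclusions. Analyse all randomized participants in their allocated group, at most leaving out those who never took a dose.
2. Apply the stated missing-data rule to every missing week-12 outcome.
3. Use protocol violations only to define the per-protocol set.
4. If any other exclusion is kept, call the set modified intention-to-treat and limit the exclusion to reasons present before randomization and judged blind to allocation.
5. As a minor matter, define the safety set by exposure alone (at least one dose), so that membership does not turn on how the safety-assessment condition is read.

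The change is one of wording and should be made before unblinding. Reported response rates would be slightly less favourable. Power would fall somewhat if many patients had no data: by 83.7 − 82.2 = 1.5 percentage points if they were 5% of each arm, and by 79.4 − 74.8 = 4.6 points if they were 15%, under the assumptions shown in the working.

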### Confirmation of case count

2.3

The sample size was calculated based on the expected reduction in serum NT-proBNP levels. Consistent with previous studies demonstrating that a > 30% reduction in NT-proBNP is associated with significantly better prognosis compared to stable or rising levels, efficacy was defined as a > 30% decrease from baseline (11). Based on preliminary research data, the efficacy rates of QSG and placebo after 12 weeks of intervention in chronic heart failure were 50% and 32%, respectively (9). Furthermore, pre-experimental studies demonstrated that QSG significantly improved cardiac function, cardiac structure, and factors related to myocardial hypertrophy in mice with transverse aortic constriction (TAC)-induced heart failure. Therefore, this study projected an efficacy rate of 53% for QSG and 33% for placebo. Given a type-I error rate of *α* = 0.05 and a type-II error rate of *β* = 0.2, and accounting for a 15% dropout rate, the required sample size was calculated using the two-sample comparison of proportions in *PASS* (version 21.0.3) software. This yielded 110 patients per group, totaling 220 cases for both groups.

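### The 80% power in section 2.3 assumes dropouts leave the analysis, but section 2.15 imputes missing outcomes by an undefined worst-case rule; power is about 75–79% if missing counts as non-response

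*Protocol article*

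**What the plan says.** Section 2.3 (Confirmation of case count) sizes the trial on the NT-proBNP responder endpoint. The rates are given as follows: "Therefore, this study projected an efficacy rate of 53% for QSG and 33% for placebo". The error rates are α = 0.05 and "a type-II error rate of *β* = 0.2", and the size was obtained "accounting for a 15% dropout rate, the required sample size was calculated using the two-sample comparison of proportions". The result is 110 per group, 220 in total. Section 2.12.1 fixes the endpoint as binary: "The main primary outcome is the NT-proBNP responder rate at week 12, defined as a decrease in NT-proBNP exceeding 30% from baseline".

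Section 2.15 (Data analysis and statistical methods) sets the missing-data rule for the primary analysis: "For missing co-primary endpoint data, the prespecified conservative worst-case approach will be used in the primary FAS analysis". The rule is not described further. Multiple imputation is a sensitivity analysis, "with additional best/worst-case analyses to evaluate departures from that assumption". The same paragraph removes from the FAS participants with a major protocol violation, no exposure to study drug, or no data at all after randomization.

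**The concern.** Dividing an evaluable sample size by 0.85 is the right inflation when dropouts contribute nothing to the test and the remaining participants show the full planned difference. When dropouts stay in the analysis with an imputed outcome, the number analysed is larger but the difference is smaller. The two effects do not cancel, so the power in 2.3 belongs to a different analysis from the one in 2.15.

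How far the difference shrinks depends on what worst case means. For a responder endpoint there are two common readings: missing counts as non-response in both arms, or missing counts against the test product in each arm (failure on QSG, success on placebo). The first costs a few points of power. The second could nearly erase a true effect of the planned size. If the choice were still open when the data are unblinded, it could decide the result.

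**Working it through.** **Inputs.** Rates 0.53 and 0.33, α = 0.05, β = 0.2, 15% dropout, 110 per arm (section 2.3); two-sided testing (section 2.15: "All statistical tests will be two-tailed"); 1:1 allocation (section 2.9).

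**Step 1: reproduce 110.** Two-proportion z formula with unpooled variance:

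n = (1.96 + 0.8416)² × (0.53×0.47 + 0.33×0.67) / 0.20² = 7.849 × 0.4702 / 0.04 = 92.3, so 93 per arm.

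93 / 0.85 = 109.4, so 110. The match is exact. Pooled variance gives 96, then 113; the arcsine form gives 95, then 112. The stated figure is sound for an analysis of about 93 completers per arm.

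**Step 2: power if dropouts are removed.** For the uncorrected chi-square test:

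power = Φ[(d − 1.96·SE₀) / SE₁], with SE₀ = √(2p̄(1−p̄)/n) and SE₁ = √((p₁(1−p₁) + p₂(1−p₂))/n).

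With n = 110 × 0.85 = 93.5 and 0.53 versus 0.33, power is 79.4%. The small gap from 80% comes from pooled rather than unpooled variance.

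**Step 3: missing = non-response in both arms, all dropouts kept.**
- Rates: 0.85×0.53 = 0.4505 and 0.85×0.33 = 0.2805, so d = 0.17.
- p̄ = 0.3655, SE₀ = 0.0649, SE₁ = 0.0639.
- Power = Φ[(0.17 − 0.1273)/0.0639] = Φ(0.67) = 74.8%. Exact binomial enumeration gives 75.1%.
- About 125 per arm would be needed for 80%.

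**Step 4: missing QSG = failure, missing placebo = success, all dropouts kept.**
- Rates: 0.4505 and 0.2805 + 0.15 = 0.4305, so d = 0.02.
- p̄ = 0.4405, SE₀ = 0.0669, SE₁ = 0.0669.
- In favour of QSG: Φ[(0.02 − 0.1312)/0.0669] = Φ(−1.66) = 4.8%.
- In favour of placebo: 1.2%. Both tails together: 6.0%.

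**Step 5: allow for the FAS exclusions.** The article does not say what share f of the 15% would be excluded, so f is an assumption shown over its whole range. The number analysed per arm is 110(1 − 0.15f), and the missing fraction among them is 0.15(1 − f)/(1 − 0.15f).

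| Share of dropouts excluded from FAS | Non-response in both arms | Arm-asymmetric rule (QSG benefit) |
|---|---|---|
| 0% | 75% | 5% |
| 25% | 76% | 14% |
| 50% | 77% | 31% |
| 75% | 78% | 56% |
| 100% | 79% | 79% |

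**Step 6: vary the missing rate, all dropouts kept.**

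| Missing in each arm | Non-response in both arms | Arm-asymmetric rule (QSG benefit) |
|---|---|---|
| 5% | 82% | 55% |
| 10% | 79% | 22% |
| 15% | 75% | 5% |
| 20% | 71% | 0.5% |

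**The case against.** Several stronger inferences are tempting, and the article does not support them.

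**That the primary analysis has about 5% or 6% power.** Section 2.15 nowhere says that missing placebo outcomes count as successes. Non-response in both arms is an ordinary conservative rule for a responder endpoint. The 6% also includes rejections in favour of placebo. The asymmetric figures show what the wording leaves open, not what the plan does.

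**That one rule serves as both primary and sensitivity analysis.** That follows only if worst case means the same in both sentences. The best/worst-case analyses are introduced as additional to the primary rule, which suggests that they differ from it.

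**That every dropout is kept.** The FAS exclusions would remove some of them, as section 2.3 assumes. The figures with all dropouts retained are the low end of a range.

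**That the sample size arithmetic is wrong.** It reproduces exactly.

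Two further objections carry weight. First, the article does not say how the study behind the 53% and 33% handled missing values. If those rates already counted missing participants as failures, analysing all 110 per arm would give about 85% power. That the rates apply to completers is inferred from the dropout inflation, which would be unnecessary otherwise. Second, the rule is called prespecified, so a full protocol or analysis plan may define it, and an article may leave such a definition there. What remains does not depend on that document: the article itself states both the basis of its power and a primary imputation rule, and under the assumptions used here either reading of the rule lowers the power while dropouts remain in the FAS.

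**Conclusion.** The point holds as a mismatch between the stated power and the stated primary analysis, made worse by an imputation rule with two incompatible readings. If missing counts as non-response in both arms, power is about 75–79% against the planned 80%, a loss of at most 4 to 5 points when variances are treated alike (79.1% to 74.8% pooled, 80.3% to 75.8% unpooled, starting from 93 per arm). If the rule were arm-asymmetric, power to show a QSG benefit would range from about 5% to 79% with the share of dropouts excluded from the FAS, and would be about 31% at one half. The modest loss alone would be minor. The reason to act is that the wording does not rule out a primary analysis that could nearly erase a true effect.

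These figures assume 53% versus 33% among completers, 15% missing in each arm, and missingness unrelated to outcome. They cover the NT-proBNP responder endpoint only. The article gives no planning figures for the six-minute walk test, which the same co-primary rule covers.

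**What to change.** - **Section 2.15, primary rule.** State that FAS participants without a week-12 NT-proBNP value count as non-responders in both arms.
- **Section 2.15, sensitivity analyses.** Keep the arm-asymmetric best-case and worst-case bounds, alongside multiple imputation, as sensitivity analyses only, and say for each bound how missing values are set in each arm.
- **Section 2.3.** State that 53% versus 33% is assumed among completers, and that power for the NT-proBNP responder endpoint with 110 per arm is about 75–79% at 15% missing, depending on how many dropouts remain in the FAS.
- **Six-minute walk test.** Give it its own arm-symmetric missing-data rule.

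The changes should be made before unblinding. They cost wording and a slightly less favourable stated power, and add no patients.

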## Discussion

3

HFrEF represents a severe manifestation or end-stage condition of various cardiac diseases (13). Long-term hypertension predisposes to pathological changes such as ventricular remodeling, leading to heart failure with reduced ejection fraction (14). Although ACEIs/ARBs, beta-blockers, and SGLT2 inhibitors have become cornerstones of standard HFrEF therapy, long-term patient outcomes remain suboptimal with persistently high readmission rates (15, 16). CM demonstrates favorable effects on long-term efficacy and readmission rates in heart failure, though individual responses vary considerably.

Based on CM theory, we integrate the primary symptom clusters of HErEF—restlessness, dyspnea, chest tightness, cold extremities, orthopnea, lethargy, edema, dry mouth with bitter taste, sallow complexion, jugular vein distension, cyanosis of lips and nails, palpitations, fatigue, oliguria, elevated high-sensitivity C-reactive protein (CRP), elevated interleukin (IL)-6, and elevated neutrophil-to-lymphocyte ratio (NLR) in patients with hypertension and HErEF. We propose a “toxic” state in these patients and developed the compound formula QSG with “Yiqi Jiedu” functions for heart failure treatment. Preliminary studies confirmed the efficacy and safety of QSG, but high-quality clinical evidence regarding its therapeutic effect in hypertension associated HFrEF remains lacking. Therefore, with support from the Ministry of Science and Technology, we conducted this multicenter, double-blind, randomized placebo-controlled trial to investigate the efficacy and safety of QSG in hypertension associated HFrEF patients.

The primary characteristic of HFrEF is reduced exercise tolerance resulting from impaired cardiac and vascular function. Dyspnea and fatigue are the main manifestations of exercise intolerance and also hallmark symptoms of HFrEF. This study employs the six-minute walk test as one of the primary outcome measures to objectively assess exercise tolerance in hypertension associated HFrEF patients. Additionally, we selected the change in NT-proBNP from baseline to the end of treatment as a key outcome indicator. As the most valuable and reliable laboratory biomarker for heart failure recommended by guidelines, NT-proBNP is characterized by ease of measurement, accuracy, and reproducibility (17, 18). It is commonly used to diagnose heart failure, stratify risk, and evaluate the clinical efficacy of medications.

NYHA cardiac function classification serves as a widely accepted indicator for assessing impaired cardiac function (19, 20). Echocardiography accurately reflects ventricular remodeling and cardiac function status (21), making it one of our secondary outcome measures. Additionally, this study comprehensively evaluated patients’ living conditions, social quality, and physical changes. Therefore, the KCCQ and the Heart Failure Toxic Syndrome Quantification Scale were also considered as secondary outcome measures.

This study involves multiple participating institutions, making quality control one of our primary challenges. We established Standard Operating Procedures (SOP) and provided extensive training to all investigators/physicians prior to patient recruitment. Through initial, supplemental training, and ongoing review, we ensured proper execution of SOP to guarantee data collection quality. Furthermore, we prioritized patient communication to ensure all participants had a thorough understanding of the trial, enabling strict adherence to requirements and attendance at all scheduled appointments.

This study design strictly adheres to the CONSORT guidelines employing a multicenter, randomized, double-blind, placebo-controlled trial design to minimize bias (22). The sample size calculation is scientifically sound, with a follow-up period extending to 52 weeks, enabling thorough assessment of long-term efficacy and safety outcomes. Furthermore, we incorporated readmission rates as a late-stage follow-up indicator, directly linking to health economics metrics, thereby demonstrating strong clinical and practical significance. We anticipate this clinical trial will provide high-level evidence-based medical evidence for the application of traditional Chinese medicine in the field of hypertension-related heart failure.
